### Prognostic measures

Prognostic measures and potential confounders were searched for in the literature [16,31,32]. The following prognostic measures were selected and will be taken into account as potential confounders (table 1): I) personal characteristics: (a) gender, (b) age, (c) disorder severity, based on mental health symptoms (DASS, HADS), (d) work relatedness of sick leave on the moment of inclusion, e) total days of sick leave in the year before the inclusion (figure 1); II) treatment characteristics: (f) treating OP, (g) guideline adherence by the OP, (h) referral behaviour of the OP; III) work characteristics: (i) type of function (executive vs. administrative), (j) working hours (part-time vs. full-time), and (k) police department (Zaanstreek-Waterland vs. Hollands Midden).

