## Methods/Design

### Study design

In a randomized controlled trial (RCT) the effect of the 'Dutch national guideline on the management of employees with mental health problems by OPs' was evaluated. The focus of this study is to examine the new, more active role of Dutch OPs according to the new guideline. Therefore, subjects in the intervention group were treated by OPs, who were trained to provide treatment according to the guideline. The control group received usual care, with minimal involvement of the OP and if applicable, access to treatment by a psychologist.

The first hypothesis of this study is that the intervention will lead to health gain for employees on sick leave due to common mental health problems. This will result in faster recovery, less stagnation and less referrals to psychologists. Counseling, instead of symptom based treatment, will result in earlier return to work and consequently a decrease of productivity loss. The second hypothesis is that the intervention will additionally lead to relatively more treatment satisfaction of the employee, the employer and the OP. The third hypothesis is that a decrease of productivity loss and prevention of expensive referrals to secondary care, will reduce costs.

The recruitment of participants for the study started in January 2002 and ended in January 2005. There was a one year follow-up. The study was funded by the Dutch Ministry of Internal Affairs and Kingdom Relations, and the Insurance Agency on Medical Guidance of the Dutch Police (DGVP). The study design, protocol and procedures were approved by the Medical Ethics Review Committee of the VU University Medical Centre.

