### Interventions

#### Usual care

In this study the aim was to compare usual care of employees with mental health problems with an intervention. Usual care consisted of minimal involvement of the OP and access to treatment by a psychologist, as this represents daily practice. As the aim was to deliver the best optional care to our study population, optimal usual care was provided in this study. This consisted of the advice to OPs to refer to a psychologist, whose treatment was fully funded by the DGVP. The OP could refer to a psychologist working for a commercial multidisciplinary rehabilitation center, i.e. De Gezonde Zaak (DGZ), as this was part of an agreement with the OHS Commit. A patient was only referred if according to the expert judgement of the OP this made sense to the health condition of this person.

DGZ is one of the largest Dutch commercial psychotherapeutic intervention centers, which focuses on return to work of the employee. DGZ is located in different parts of the country. Besides physical therapists, around 100 psychologists are working for this organization. The psychologists are working according to cognitive behavioral principals. The standard therapy offered was based on protocols of the Dutch Institute for Work and Stress [20].

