#### Co-interventions

Co-interventions cannot always be avoided. In case of post traumatic stress disorders, patients were also referred to a specialized trauma centre according to a special protocol of the DGVP. As the rehabilitation centre DGZ worked with multiple disciplines, it is possible that some patients in the control group received a combined intervention for mental and physical complaints by a psychologist and a physical therapist. In both the intervention and control groups co-interventions were registered in the medical files of the OHS and the database of the DGVP. These data can be used to adjust for co-interventions in the final multivariate analyses.

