**Data related to prognostic measures**						

I) Personal characteristics						
Gender, Age	Database company	X				
Severity disorder: DASS/HADS (effect modifier)	Questionnaires		X			
Work-relatedness of the disorder	Medical files OHS	X				
Sick leave in year before inclusion (effect modifier)	Database company	X				
II) Treatment						
Treating occupational physician (OP)	Medical files OHS	X				
Diagnosis made by the OP	Medical files OHS	X				
Guideline adherence of the OP	Medical files OHS	X	X	X	X	
III) Work characteristics						
Type of function	Database company	X				
Number of working hours	Database company	X				
Police constabulary	Database company	X				

Another primary outcome variable that is part of the RTW process is first RTW: i.e. the duration of sick leave due to mental health problems in calendar days to first (partial or full) return to own or equal work. Other variables are related to recurrences of sick leave periods in the one year follow-up (T4)(table 1). These variables are the time in calendar days until the first recurrence of sick leave takes place and the number of and days during recurrences [21]. Total days of sick leave during follow-up is a primary outcome variables as well.

There was double registration of sick leave data, as both the employer and the OHS have their own registration system. The aim was to compare data of both systems, with the sick leave data of the employer as the 'golden standard'. This additional effort was done as reliable sick leave data are hard to get, since there is a known discrepancy with self-reported sick leave [24,25].

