### Data analysis

All analyses will be conducted according to the intention-to-treat principle and will be performed on the patient level. To examine the success of randomization, descriptive statistics will be used to compare the baseline measurements of the two groups. If necessary, analyses will be adjusted for prognostic dissimilarities.

The evaluations on the effectiveness of the guideline compared to usual care will be performed with two tailed tests at a significance level of 5% (P < 0.05). To examine differences in the data on RTW, we will use Kaplan Meier's and the Cox proportional hazard regression for recurrent events. The general idea behind this analysis is that the different time periods are analysed separately adjusted for the fact that the time periods within one patient are dependent. Recurrences of sick leave for any reason during follow-up will be added to the Cox proportional hazards model with the time to event approach, in which only the transitions from no treatment success (sick leave) to treatment success (full RTW) are taken into account [38].  In this model, the state of sick leave until the moment of inclusion will be added as a covariate. Number and days of sick leave periods in the year before inclusion will be added as a potential effect-modifier.

In a linear regression model treatment satisfaction during treatment (T2) and after treatment by the OP (T3) will be measured as respectively a short term and a long term effect and differences will be compared between the groups. Treatment satisfaction at the start of the treatment (T1) will be added as a covariate, even as the treatment group to examine differences in effects between the groups. The levels of treatment satisfaction of both the employees and their supervisors will be compared for the different moments with a chi-square test. Pair-wise correlations will be used to compare treatment satisfaction of the employee and their supervisor on the different moments.

In the Cox and linear regression models potential treatment differences by the OPs and their OHSs will be taken into account by means of nested dummy variables. The police constabulary the employee works for, will be put into the model as a binomial variable. Differences in sick leave patterns in the year before inclusion and in the severity of the mental health problems (DASS/HADS-scores) will be put into the model as potential effect modifiers.

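### Guideline adherence and referral arise after allocation, yet the plan lists them as potential confounders; adjusting for them would replace the intention-to-treat effect with a different quantity

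*Protocol article*

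**What the plan says.** All references are to the protocol article.

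- **Prognostic measures.** The listed variables "were selected and will be taken into account as potential confounders". Beside gender, age and work characteristics the list has "II) treatment characteristics: (f) treating OP, (g) guideline adherence by the OP, (h) referral behaviour of the OP". The abstract repeats the confounder role for prognostic measures in general.
- **Co-interventions.** On care recorded in both arms during the trial: "These data can be used to adjust for co-interventions in the final multivariate analyses".
- **Study design.** The first hypothesis about the intervention includes an effect on referral: "This will result in faster recovery, less stagnation and less referrals to psychologists".
- **Usual care.** Of the optimised control care: "This consisted of the advice to OPs to refer to a psychologist".
- **Data analysis.** All analyses follow intention to treat. The named model terms are sick leave up to inclusion, sick leave in the prior year, OP and OHS, police constabulary, and DASS/HADS severity. After a descriptive comparison of baseline measurements comes a general clause: "If necessary, analyses will be adjusted for prognostic dissimilarities".
- **Later in Data analysis, and in the Discussion on contamination.** Adherence is also given a process-evaluation and per-protocol role.

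**The concern.** In a randomised comparison a confounder cannot be a consequence of allocation. Adherence to the guideline is how the intervention is delivered, and referral behaviour is something the intervention is meant to change. Placing both in one list with gender and age treats parts of the treatment effect as background differences between patients.

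A return-to-work model that holds them fixed asks what allocation does among patients who received the same care. That is not the question of the trial. The effect that passes through the adjusted variables is removed. If severity or slow recovery also drives these variables, a non-randomised comparison is brought in as well. The primary estimate is at stake.

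**Working it through.** The plan gives no figure on this point, so there is none to reproduce. The check sets the passages side by side and then illustrates the size on assumed rates.

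**1. Timing.** Under Recruitment and selection, the OP opens the envelope at T0, after consent. In Table 1 the row "Guideline adherence of the OP" is collected from T0 through T3, and Table 5 scores it over successive consultations. Referral is likewise a decision made during care.

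**2. What the variables measure.** The Compliance section uses adherence and the proportion referred as the measures of OP compliance. The text after Table 5 counts adequate adherence as compliance in the intervention arm and deviant adherence as compliance in the control arm. So (g) records treatment received. The section on guideline adherence expects training to act on outcomes through OP skills, and Study design expects fewer referrals. Both variables are on the plan's own causal path.

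**3. Dependence on recovery.** The Contamination section says that the guideline favours referral when recovery stalls or problems are severe. In Table 5, indicator 9 does not apply once the patient is partly or fully back at work, and the follow-up criterion of indicator 10 applies only while recovery is incomplete. Slow recovery can therefore change both variables, and conditioning on them partly conditions on severity and on the outcome.

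**4. Size for referral (assumed rates).** HR above 1 means faster return to work in the intervention arm. Let pC and pI be the referral proportions (control, intervention), r the hazard multiplier of referral, and d the effect of allocation by other routes. Then, approximately,

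unadjusted HR = d × [1 + pI(r − 1)] / [1 + pC(r − 1)]; HR with referral in the model = d.

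- pC 0.8, pI 0.2, r 0.6, d 1: 0.92 / 0.68 = 1.35, against 1.00 adjusted. Cox simulations with 8,000 per arm and censoring at 365 days gave 1.32 to 1.35, and 1.00.
- pC 0.6, pI 0.4, r 0.6, d 1: 0.84 / 0.76 = 1.11, against 1.00 adjusted.
- pC 0.8, pI 0.2, r 1.4, d 1.4: 1.4 × 1.08 / 1.32 = 1.15, against 1.40 adjusted. Here adjustment moves the estimate away from 1.

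**5. Size for adherence (assumed rates).** The simulation used 107 per arm (the plan's number before dropout), mean baseline duration 180 days, censoring at 365 days, 300 runs per row, and a total log HR of ln 2 = 0.69 split between adherence and a direct effect. With half direct, the expected adjusted HR is exp(0.5 × 0.69) = 1.41.

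| Adequate adherence, intervention vs control | Share through adherence | HR, arm only | Rejection | HR, adherence added | Rejection |
|---|---|---|---|---|---|
| 90% vs 10% | all | 1.95 | 99% | 0.99 | 5% |
| 80% vs 20% | all | 1.86 | 99% | 1.02 | 5% |
| 70% vs 30% | all | 1.64 | 92% | 1.00 | 6% |
| 90% vs 10% | half | 2.01 | 100% | 1.42 | 30% |
| 80% vs 20% | half | 1.95 | 100% | 1.41 | 49% |
| 70% vs 30% | half | 1.87 | 100% | 1.42 | 61% |

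Part of the power loss is collinearity: at 90% vs 10% the standard error of the arm term rises from 0.15 to 0.25. These runs contain no shared cause of adherence and outcome, so the distortion in step 3 would come on top.

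**The case against.** The best defence is that the analysis section never puts (g) or (h) into an effect model. Its named terms omit both, its general adjustment clause follows a comparison of baseline measurements and so is aimed at baseline imbalance, and adherence has a proper separate role in the process and per-protocol analyses. This stands in part: the harm is conditional. It does not clear the point, because nothing withdraws the confounder label, and the analysis section does not limit adjustment to pre-allocation variables. The list is a positive statement, not detail left to a fuller document.

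Four stronger readings are tempting, and the document does not support them.

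- *Co-interventions are listed as confounders and are the treatment contrast.* They are not in the list. The co-intervention sentence is permissive, and its examples (a trauma centre, added physical therapy) are ancillary care. They still arise after allocation.
- *Referral simply is the control treatment.* Control referral depended on OP judgement, and indicators 6 and 8 of Table 5 accept referral as adequate guideline care in some cases. It is a compliance measure and a hypothesised effect, but not a clean marker of arm.
- *Adjustment always biases towards no effect.* The third referral scenario shows the opposite, and the fall to 1.00 follows from assuming that nothing acts outside the adjusted variable.
- *Adjustment would be chosen by baseline significance tests.* The plan describes descriptive statistics.

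Treating OP, item (f) in the same list, is not at fault.

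**Conclusion.** The point holds in conditional form. The plan designates two post-allocation measures of care as potential confounders and allows adjustment for a third kind, while promising intention to treat. If those statements are followed, the arm coefficient does not estimate the promised effect. That conclusion rests on the document's own timing and definitions and needs no assumed rate.

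The size does need assumptions. Under full mediation the effect vanishes (illustratively HR about 1.3 to 1.0 for referral, or 1.6 to 1.95 down to about 1.0 for adherence). Under half mediation it falls from about 1.9 to 2.0 to about 1.4. If referral speeds return to work, or if severity or slow recovery drives referral and the adherence scores, the distortion can go either way. A reader might infer that the primary model is certain to contain these terms, or that a true benefit is certain to be lost. The document supports neither.

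**What to change.** 1. Remove (g) and (h) from the list of potential confounders.
2. Withdraw the option to adjust the effect models for co-interventions.
3. State in Data analysis that adjustment in the intention-to-treat models uses only variables fixed before the envelope is opened, and name them in advance: for example treating OP, police department, age, gender, work-relatedness, type of function, working hours, prior-year sick leave and sick-leave days before T0.
4. Keep DASS/HADS severity in its planned role with a caveat. Data collection places these questionnaires at T1, after consent and allocation, and the Discussion concedes that the inclusion consultation may have altered the answers.
5. Report adherence, referral and co-interventions in the process and per-protocol analyses, or in a mediation analysis labelled exploratory.

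The cost is a change of wording in three sections. No new data are needed, because every variable is already collected.

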#### Depression Anxiety Stress Scale (DASS)

To measure mental health complaints at baseline in this study, the Depression Anxiety Stress Scales (DASS) were used [33]. The structure of the DASS seems to support the view that both anxiety disorders and depression need to be distinguished from adjustment disorders in spite of their communality. The psychometric properties of this instrument appear to be sound enough to be applied to both healthy and psychiatric populations. Therefore, the psychometric properties of the DASS are suitable for use in an occupational health care setting. Moreover, convergent and divergent validity have been shown to be satisfactory [34].

The employees participating in this study filled in a self-report questionnaire that comprises the DASS-42, which takes 7 minutes to complete. The DASS-42 consists of 42 symptoms divided into three subscales of 14 items: depression scale, anxiety scale, and stress scale. Participants rated at baseline the extent to which they had experienced each symptom over the previous week on a four point Likert scale ranging from 0 (did not apply to me at all) to 3 (applied to me very much, or most of the time).

Based on the results of their study on employees with mental health problems in occupational health care, Nieuwenhuijsen et al. [34] developed cut-off scores to divide the DASS-rates into four categories: stress, depression, anxiety, and depression/anxiety. The cut-off scores are > 12 on symptoms of depression and > 5 on symptoms of anxiety.

#### Hospital Anxiety Depression Scale (HADS)

The HADS is a 14-item screening scale that measures the presence of anxiety and depressive states [35]. It contains two 7-item subscales: a depression subscale and an anxiety subscale, each item being scored on a four point Likert scale (0–3) that applies to the previous week. The HADS has been developed as a screen for detecting depressive and anxiety disorders in hospitalised patients. Items referring to symptoms that may have a physical cause (for example, weight loss or insomnia) are not included in the scale. Because a higher rate indicates more mental health symptoms, item 1,3,5,6,8,10,11 and 13 will be recoded.

The HADS is easily administered as a self-report measure as it usually takes 3–5 minutes to complete. A total score (out of a possible 21) for each subscale is then calculated. Zigmond et al. [35] recommended cut-off points with scores less than eight on either of the two subscales to be non-cases and scores between eight and ten as borderline cases.

#### Guideline adherence by the OP

The aim of this study is to examine the effectiveness of the management by Dutch OPs, under the expectation that (training in) the guideline will lead to additional skills for the OP and consequently to positive outcomes. To explore our hypothesis that the guideline leads to additional skills and outcomes, we examined the performance by the OP according to the guideline (guideline adherence). Guideline adherence by the OP was checked by means of an audit of the medical files. Guideline adherence was defined as the total score on ten validated performance indicators for the treatment of each participant by the OP (table 5)[11,18,36]. For each performance indicator, we used validated criteria. If a criterion was not met, the case was assigned 1 for that performance indicator. If all applicable criteria for a performance indicator were met, the resulting score was 0 for that case. The medical files of all the participants were assessed on if they met the criteria of the different indicators (0=adequate care; 1=deviant care). In this way an average performance rate was obtained for each performance indicator. Furthermore, a total score of all performance indicators was calculated (guideline adherence). Guideline adherence was dichotomized into adequate adherence and deviant adherence. Adherence was considered deviant if three or more performance indicators were assigned a score of 1, and adequate if less than three performance indicators had a score of 1.

**Table 5 T5:** Performance indicators guideline adherence and their criteria 1 = deviant care, NA = Not applicable

**PI 1**	**Assessment of symptoms**	**Score**
Criteria:	1. Presence or absence of essential symptoms of anxiety disorder and depressive disorder should be noted in file	
	2. Presence or absence of distress symptoms (fatigue, concentration problems, sleeping problems, and emotional reactivity) should be noted in file	
	*One or both criteria not met within 2 consultations?*	PI1 = 1

**PI 2**	**Correct diagnosis**	

Criteria:	1. Diagnosis should be noted in file	
	2. Diagnosis should be correct:	
	- IF adjustment disorder: at least one psychological distress symptom should be noted in file	
	- IF depressive disorder: at least one essential symptom AND five depressive symptoms should be noted in file	
	- IF anxiety disorder: at least one anxiety disorder should be noted in file	
	3. Diagnosis should not be missed if criteria above apply	
	*One or more criteria not met within 2 consultations?*	PI2 = 1

**PI 3**	**Evaluation curative care**	

Criteria:	1. Treatment in the curative sector, or its absence, should be noted in file	
	2. IF patient receives treatment, THEN the OP should evaluate whether this treatment is effective	
	*One or both criteria not met within 2 consultations?*	PI3 = 1

**PI 4**	**Assessment work-related causes**	

Criteria:	1. the work-related causes, or their absence, should be stated in file	
	*One or both criteria not met within 2 consultations?*	PI4 = 1

**PI 5**	**Evaluation of work disabilities**	

Criteria:	1. Functional limitations in home or work environment, or their absence, should be stated in file.	
	2. Work activities of patient should be noted by OP	
	3. OP should assess whether patient is limited in his work functioning	
	4. IF patient has work limitations, THEN OP should assess other impediments for return to work (such as problems in home situation or with supervisor)	
	One or both criteria not met within 2 consultations?	PI5 = 1

**PI6**	**Interventions targeted at individual**	

	1. Intervention aimed at the individual should be noted or be referred - IF adjustment disorder, THEN OP should start interventions OR should refer patient to psychologist/social worker/general practitioner OR should consult with practitioner giving current treatment - IF anxiety disorder OR depression OR other psychiatric disorder, THEN OP should refer patient to psychologist/social worker/general practitioner OR should consult with practitioner giving current treatment	
	*Criterion not met within 3 consultations?*	PI6 = 1

**PI7**	**Interventions targeted at organisation**	

	IF work is a causal, eliciting or maintaining factor in the mental health problem, THEN OP should intervene in the work organisation (confer with supervisor/personnel officer)	
	*Criterion not met within 3 consultations?*	PI7 = 1
	*IF work is neither causal, eliciting nor maintaining factor in mental health problem*	PI7 = NA

**PI8**	**Interventions targeted at providers of care in curative sector**	

	1. IF treatment in curative sector is lacking and deemed necessary, THEN OP should start interventions targeted at the individual OR refer patient to psychologist/social worker/general practitioner	
	2. IF treatment in curative sector is not effective, THEN OP should consult with practitioner giving current treatment	
	*One or both criteria not met within 3 consultations?*	PI8 = 1
	*IF patient receives effective treatment in curative sector*	PI8 = NA

**PI9**	**Advice on return to work**	

	1. Advice on return to work should be provided by OP	
	2. IF no impediments for return to work are present, THEN OP should advise full or partial return to work	
	*One or both criteria not met at each consultation?*	PI9 = 1
	*Patient already (partially) returned to work?*	PI9 = NA

**PI10**	**Timing of consultations**	

	1. First consultation should be within 3 weeks from first day of sickness absence	
	2. IF patient has not yet completely recovered, THEN next consultation should be within 4 weeks from previous consultation	
	*Criterion 1 not met at first consultation OR criterion 2 not met at consultation 2 or 3?*	PI10 = 1

Additionally, this audit gave us information about treatment compliance by the OP (guideline adherence) in both groups. In this way contamination between the study groups was studied as well. Adherence in the intervention group was considered compliant if there was adequate adherence. Guideline adherence in the control group was considered compliant if there was deviant adherence.

The performance indicators will be assessed on their criteria by three independent researchers, resulting in a dichotomised score on guideline adherence for each employee (adequate versus deviant).

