To assess whether protocol deviations will cause bias, the results of the intention-to-treat analyses will be compared to per-protocol analyses. A process evaluation will be done, based on the assessment of guideline adherence by means of performance indicators [18]. For each performance indicator potential effects on our primary outcomes will be measured.

Indirect costs can be calculated using the friction cost approach (friction period 122 days) and the human capital approach, based on income as provided by the employer or as derived from function, age and gender [30]. Bootstrapping will be used for pair wise comparison of the mean groups to calculate mean differences and confidence intervals in costs and cost-effectiveness ratios for all interventions. All these analyses will be conducted in SPSS 14.0, Excel and, if necessary, in Strata.

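### Judging compliance and contamination on a yes/no adherence label discards information that the ten-indicator total already holds; comparing the arms on the total would be a cheap improvement

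*Protocol article*

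**What the plan says.** All references are to the protocol article. Under Guideline adherence by the OP, the measure starts as a count: "Guideline adherence was defined as the total score on ten validated performance indicators for the treatment of each participant by the OP". Each indicator scores 1 for deviant and 0 for adequate care. The count is then split: "Adherence was considered deviant if three or more performance indicators were assigned a score of 1, and adequate if less than three". The same section says that three researchers will assess the files, "resulting in a dichotomised score on guideline adherence for each employee (adequate versus deviant".

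The label then defines compliance, in opposite directions for the two arms: "Adherence in the intervention group was considered compliant if there was adequate adherence" and "Guideline adherence in the control group was considered compliant if there was deviant adherence". The section adds that contamination was studied through the same audit.

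Table 5 allows PI7, PI8 and PI9 to be not applicable, so between seven and ten indicators are scored per file. The threshold of three does not change with that number.

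Other parts of the article also bear on the point:
- Guideline adherence by the OP keeps an average rate for each indicator.
- Compliance adds a second measure, the proportion referred to the study's psychologist centre in each arm.
- Data analysis states "A process evaluation will be done, based on the assessment of guideline adherence by means of performance indicators", and its next sentence relates each indicator separately to the primary outcomes.
- Data analysis and Contamination between study groups plan per-protocol analyses.

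**The concern.** Two and three deviant indicators are treated as opposite care, while three and nine are treated as the same care. If most files in both arms have three or more deviant indicators, the percentages labelled deviant crowd towards 100% and can look alike even though control care is further from the guideline.

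This matters because the same trained OPs treat both arms, and the article itself names contamination as a risk. If return to work does not differ, the reader will ask whether the guideline failed or whether the arms received much the same care. The adherence audit is one of the two measures the article offers for that question. A blunt version of it makes a real difference in care harder to see.

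The fixed count adds a second weakness. Two files with the same underlying rate of deviant care have different chances of the label if different numbers of indicators apply.

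**Working it through.** **The plan's own figure.** Study population: sample size and power analysis gives 107 per group and 20% dropout. 107 / 0.80 = 133.75, rounded up to 134; 2 × 134 = 268, as stated. The article gives no power or effect size for the adherence comparison. I use 107 per arm and the two-sided 5% level from Data analysis.

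**Assumptions.** The article gives no deviance rates, so these are assumed over a range. Let p be the chance that an applicable indicator is deviant, m the number of applicable indicators, and r the correlation between indicators within a file. The count is beta-binomial with mean mp and variance mp(1−p)[1 + (m−1)r].

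**Power formulas** (normal approximation, n per arm; Φ is the standard normal distribution function):
- Total: Φ( Δmean / √[(V1 + V2)/n] − 1.96 ).
- Cut: with d = P(count ≥ 3) in each arm and d̄ their average, Φ( { d2 − d1 − 1.96 √[2d̄(1−d̄)/n] } / √[(d1(1−d1) + d2(1−d2))/n] ).

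**One case in full:** m = 10, r = 0.1, intervention p = 0.40, control p = 0.48.
- Total: V1 = 10 × 0.40 × 0.60 × 1.9 = 4.56; V2 = 10 × 0.48 × 0.52 × 1.9 = 4.74. The standard error is √(9.30/107) = 0.295. The mean difference is 0.8, and 0.8/0.295 − 1.96 = 0.75, so power is 77%.
- Cut: 73.4% v 84.2% are labelled deviant, and power is about 49%.

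**Range at m = 10, r = 0.1** (power with the cut / power with the total, %):

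| Intervention p | +0.06 | +0.08 | +0.10 | +0.15 | +0.20 |
|---|---|---|---|---|---|
| 0.20 | 51 / 67 | 75 / 88 | 90 / 97 | 100 / 100 | 100 / 100 |
| 0.30 | 41 / 57 | 63 / 81 | 80 / 94 | 98 / 100 | 100 / 100 |
| 0.40 | 31 / 53 | 49 / 77 | 65 / 92 | 92 / 100 | 99 / 100 |
| 0.50 | 22 / 52 | 34 / 77 | 47 / 92 | 74 / 100 | 89 / 100 |

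For differences of 0.06 to 0.10 the cut gives 22-90% and the total 52-97%, a gap of 7 to 45 points. At 0.20 the gap is 0 to 11 points.

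**Sensitivity to r**, same rates, differences 0.06 to 0.10:
- Independent indicators: 22-99% with the cut, 80-100% with the total.
- r = 0.2: 20-78% with the cut, 38-90% with the total.
- A large loss persists at a 0.20 difference in one corner. With independent indicators and intervention p = 0.50, the cut gives about 65% and the total about 100%.

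**Effect of indicators that do not apply.** With p = 0.30 and independent indicators, P(count ≥ 3) = 1 − P(0) − P(1) − P(2):
- m = 10: 1 − 0.028 − 0.121 − 0.233 = 0.62.
- m = 7: 1 − 0.082 − 0.247 − 0.318 = 0.35.

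The threshold corresponds to 3/10 = 30% of the indicators in the first file and 3/7 = 43% in the second.

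**The case against.** The case on the other side is substantial, and much of it stands.

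- A reader might infer that the trial depends on this label alone to show contrast, so that a blunt label could suggest complete contamination. The article does not support that. Compliance also compares referral proportions, and Contamination names access to the psychologist as the means of maximising contrast. Ten per-indicator rates are kept as well, and apart from indicators that do not apply, their sum is essentially the mean total.
- A reader might infer that the adherence-outcome analysis uses the yes/no value. Data analysis states it indicator by indicator. Prognostic measures lists adherence as a potential confounder without giving its form.
- A reader might infer that the cut is arbitrary because no reason is printed. The article is condensed and cites sources for the score. Whether they supply the threshold cannot be seen, so the point rests on the information lost and not on a missing justification.
- The power loss depends on assumed rates and a modest contrast of 0.6 to 1.0 indicators out of ten. The article gives no reason to expect so small a contrast. It also states no significance test of adherence between arms, so power here is only a gauge of information.
- A per-protocol set needs a yes/no rule, so the split cannot simply be dropped.

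One part of the point survives all of this. Ten separate rates and a referral percentage do not give one estimate, with its uncertainty, of how far overall care differed. Nor do they remove the label's dependence on the number of applicable indicators.

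**Conclusion.** The point holds as a minor, inexpensive improvement. The article calculates a graded total, reduces it to a label, and judges compliance and contamination on that label without stating any analysis of the total. For small contrasts (0.06 to 0.10 per indicator) the label gives clearly less power. The loss mostly disappears near 0.20, except where adherence is poor in both arms. The size of the loss rests on assumed deviance rates and within-file correlation. The dependence on the number of applicable indicators does not rest on the contrast between arms: a fixed count of three is a different standard for seven indicators than for ten.

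The finding does not extend to the main result. Adherence is a process, compliance and prognostic measure, and the intention-to-treat return-to-work comparison does not use the label.

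**What to change.** Add one or two sentences to Data analysis:
- For the between-arm comparison of OP performance and contamination, use the number of deviant indicators out of those applicable to the file. Fit an overdispersed binomial or linear model and report the mean difference with a 95% confidence interval.
- Use the same score wherever overall adherence is related to outcome or entered as a covariate.
- Keep the adequate/deviant split to define the per-protocol set and as a descriptive percentage in each arm.

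The indicators are already scored for every file, so no new data are needed. The cost is one extra analysis and a slightly less simple headline than a percentage.
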